### Plans for collection, laboratory evaluation and storage of biological specimens for genetic or molecular analysis in this trial/future use {33}

No biological data will be collected during this study.

### Statistical methods

#### Statistical methods for primary and secondary outcomes {20a}

The statistical analysis will be performed by the Department of Biostatistics, Epidemiology, Public Health, and Health Economics of Nîmes Hospital Center using SAS statistical software, Carey, NC. A difference will be considered as statistically significant if the test gives a *p* value of 0.05 or less.

##### Description of the population included and main parameters studied

Initial data analysis will describe the sample and the population per group. The Shapiro-Wilk test will be used to determine whether or not the quantitative variables show a normal distribution. Statistical results will be presented in the form of “mean ± standard deviation” for quantitative variables showing a normal distribution, and “median and interquartile intervals” for other variables. The number and associated percentage will be given for qualitative variables.

##### Analysis of the principal endpoints

The duration of a suicide reattempt-free follow-up period (SRFFP) will be assessed in the two groups using the Kaplan-Meier method and compared by a log-rank test. This analysis will be completed by a modeling analysis to take into account clustering effects.

Indeed, in our study, randomization to treatment is done on an individual basis. However, the experimental treatment is administered to a group so that several individuals receive the intervention together by the same therapist. Observations within the group therapy will likely be correlated within groups (clustering effect). In contrast, control participants receive an individual intervention and their observations can reasonably be assumed to be independent. Either arm may also be influenced by cluster effects linked to a particular therapist. The latter clustering results in asymmetric, partially nested designs. Recently, statistical models were developed to appropriately evaluate treatment effects when using a partially nested design [29]. Based on these, we will use multilevel mixed-effects models to assess the treatment effect on the outcomes describing the suicidality:
The duration of a suicide reattempt-free follow-up period (SRFFP),The suicide reattempt during the follow-up (yes/no) by adjusting for nested effects,The C-SSRS score at 12 months by adjusting for nested effects and C-SSRS score at inclusion.

The detailed statistical plan will be provided before data extraction and unblinding.

The models will also provide valuable estimates of intracluster correlation coefficients for the different psychological outcomes of our study in the context of behavioural group therapy; these data are necessary to optimize the sample size of further studies in the area of psychological research.

##### Analysis of the secondary endpoints

Multilevel mixed-effects models will be used to assess treatment effects on the evolution of the C-SSRS score and the suicidal ideation (BSSI score) and of the psychiatric symptoms (BDI-II, BHS).

##### Guess-the-group

To control for the success of blinding, outcomes assessor responses to the “guess-the-group” question will be compared to true responses using the Kappa agreement coefficient.

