### Sample size {14}

We will test the following hypothesis: The mean time to the next suicide attempt during the follow-up period is different between the two groups. The probability of a suicide reattempt-free follow-up period (PSRFFP) according to usual care was estimated at 60% by Brown et al. [6]. In this trial, a cognitive behavioural therapy (10 sessions of individual therapy) was associated with an increase of 20% in the PSRFFP at 12 months.

In our study, the 10 sessions of individual therapy program are replaced by 6 sessions of a group therapy program. We expect a minimum benefit of 20% for this new strategy (60% in the control group versus 80% in the experimental group).

To our knowledge, no study has reported intra-class correlation coefficients associated with therapists or group therapy suicide re-attempt of the C-SSRS score. It is therefore difficult to anticipate an exact sample size that would take into account clustering effects caused by group therapy (or by therapist effects) in the primary outcome assessment.

Under the hypothesis of no cluster effects (at either the therapist or therapy-group levels) and using a log-rank test, 186 subjects are required to detect 20% difference in PSRFFP at 12 months (60% in the control group and 80% in the experimental group), with a power of 85% and a bilateral alpha risk of 5%.

Given the possibility of cluster effects, we have increased this number to 216. Taking into account an anticipated rate of 10% lost to follow-up, 240 patients will be included (120 patients per group).

Patient consulting under emergencies for suicidal behaviour are common. It is more than reasonable to expect at least one case per day per centre on average, giving a minimum potential patient pool of about 1460 patients during the proposed recruitment period. To take into account the time necessary to organize group sessions and the probability that some patients might not want to participate, we proposed an inclusion averaging 5 patients per month per centre.

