### Assignment of interventions: blinding

#### Who will be blinded? {17a}

Baseline assessments will be made before randomization, so these are blinded. Patients cannot be blinded but will be asked to not reveal their group status to anybody outside their group, not even their treating psychiatrist. Furthermore, the hypotheses tested will not be communicated to patients (i.e. the patient will not be informed on the supposed superiority of one group over another).

Therapy care providers (psychologists) cannot be blinded. In order to make assessments as objective as possible, outcome assessors (psychiatrists) will be different from the therapy providers (psychologists), and every attempt will be made to keep outcome assessors blinded to patient group status. To control for the success of blinding, a “guess-the-group” question will be addressed to outcome assessors. Outcome assessor responses will be compared to expected results due to chance. Data analysts will not be involved in trial field logistics and will be blinded. During analyses, when group assignments are first required they will only be revealed as “group A” or “group B”. Only when analyses have been completed will the exact nature of groups be revealed.

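### A single kappa of assessor guess against true arm, judged against chance, cannot tell unblinding from correct guesses drawn from the outcome

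*Protocol article*

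**What the plan says.** Under Who will be blinded? {17a}, the protocol states that "a “guess-the-group” question will be addressed to outcome assessors" and gives the benchmark: "Outcome assessor responses will be compared to expected results due to chance". The statistical section Guess-the-group names the statistic: answers to the "question will be compared to true responses using the Kappa agreement coefficient". It mentions no breakdown by arm or by outcome, no visit and no value of kappa that would count as failure.

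The guessers are psychiatrists. Implementation {16c} says that the psychiatrists who include patients are also the outcome assessors, and Outcomes {12} has a psychiatrist follow each patient for 12 months. Section {17a} withholds the study hypothesis from patients and does not say whether assessors know it. Objectives and hypothesis {7} states the expected direction: earlier and more frequent reattempts under IST.

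The planned effect, in Sample size {14}, is "60% in the control group versus 80% in the experimental group" reattempt-free at 12 months.

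**The concern.** Patients and therapists are unblinded, so assessor blinding is the main protection for the C-SSRS and for the ascertainment of reattempts. The guess-the-group item is the plan's only stated evidence that this protection held.

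An assessor with no information on allocation still sees how the patient fared and may guess from that. If the therapy works, such guesses are right more often than chance with no leak at all. Zero excess agreement is then the wrong reference for successful blinding, because one kappa adds the effect of treatment to the effect of disclosure. The problem arises in the case where the check matters most: a positive trial whose readers ask whether the assessors knew the arms.

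**Working it through.** **The plan's own figure.** The protocol gives no expected kappa. The figure that carries the 60% and 80% rates is the 186 patients before inflation. The two-proportion formula with pooled variance, two-sided 5% and 85% power gives (1.960 × √(2 × 0.7 × 0.3) + 1.036 × √(0.6 × 0.4 + 0.8 × 0.2))² / 0.2² = 92.7, so 93 per arm and 186 in total. The section attributes 186 to a log-rank test; log-rank formulas gave 177 to 197, which does not bear on this point. Then "Given the possibility of cluster effects, we have increased this number to 216", and 216 / 0.90 = 240.

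**Kappa under 1:1 allocation.** Let g1 be the proportion of GPACTS patients guessed GPACTS, and g0 the same proportion in the IST arm. Agreement is 0.5 × g1 + 0.5 × (1 − g0). Chance agreement is 0.5 whatever the overall share of GPACTS guesses. So kappa = g1 − g0.

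**Perfect blinding, every guess following reattempt status.** g1 = 0.80 and g0 = 0.60. Agreement is 0.5 × 0.8 + 0.5 × 0.4 = 0.60, and kappa = (0.60 − 0.50) / 0.50 = 0.20. GPACTS is guessed for 70% overall, so the null standard error is √(0.75 − [0.5 × 0.7 × 1.2 + 0.5 × 0.3 × 0.8]) / (0.5 × √n) = √0.21 / (0.5 × √n). That is 0.059 at n = 240 (z = 3.4) and 0.062 at n = 216 (z = 3.2).

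**Perfect blinding, only some guesses following outcome.** The rest are coin tosses. 40,000 simulated trials per row, n = 240:

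| Share of guesses following outcome | Kappa | Trials with z > 1.96 |
|---|---|---|
| 100% | 0.20 | 93% (90% at n = 216) |
| 75% | 0.15 | 69% |
| 50% | 0.10 | 36% |
| 25% | 0.05 | 11% |
| 0% | 0.00 | 2.3% |

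If reattempts prompt a guess of IST and all other guesses are coin tosses, g1 = 0.40, g0 = 0.30 and kappa is 0.10 (z > 1.96 in 37%).

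**Timing.** Assume a constant hazard reaching 80% and 60% at month 12, and every guess following outcome to date. Kappa is 0.8^(t/12) − 0.6^(t/12): 0.972 − 0.938 = 0.03 at month 1.5, 0.07 at month 3 and 0.12 at month 6.

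**True disclosure.** If 20% of patients in each arm reveal their arm and the other guesses are coin tosses, g1 = 0.2 + 0.8 × 0.5 = 0.60, g0 = 0.8 × 0.5 = 0.40 and kappa is again 0.20.

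**What separates the two.**
- *By arm*, with index 2 × P(correct) − 1: outcome-led guessing gives +0.60 for GPACTS and −0.20 for IST; disclosure gives +0.20 and +0.20. The index alone is not decisive. If 20% disclose and 75% of the other guesses favour GPACTS, then g1 = 0.2 + 0.8 × 0.75 = 0.80 and g0 = 0.60, the same pair as outcome-led guessing.
- *By reattempt status*: guesses that depend only on reattempt status are all alike within a stratum, so the arms do not differ and kappa is 0. Under disclosure unrelated to outcome, g1 − g0 stays at 0.20 in both strata.

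Strata under the planned rates and 120 per arm: 24 + 48 = 72 with a reattempt and 96 + 72 = 168 without.

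**The case against.** A reader might infer that the check will report failed blinding in a successful trial even when blinding is perfect. The documents do not support that. It would need nearly all guesses to follow outcome, a guess taken late, and a rule that any kappa significantly above zero means failure. None of these is stated. The visit may be fixed in the schedule figure, which was not available. Even in the worst case kappa averages 0.20 (95% range over trials about 0.08 to 0.32) and exceeded 0.40 in fewer than 1 in 1,000 simulated trials, so agreement is low in absolute terms.

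A reader might also infer that a trial with no treatment effect would look falsely reassuring. That fails as well: with equal outcomes in the two arms, outcome-led guessing contributes zero to kappa.

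It is also fair to say that no estimate, test or analysis population depends on kappa, that the text does not exclude reporting by arm, and that a detailed statistical plan is promised before data extraction.

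These points limit the size of the concern but do not remove it. The article does not leave the choice open: it names the statistic and the benchmark. With that pair, an effective therapy under intact blinding and a real leak can give the same result.

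**Conclusion.** The point holds as a limit on what the check can show. If GPACTS works as planned, intact blinding can give a kappa anywhere from 0 to about 0.20, according to how many guesses follow outcome and when they are made. A kappa in that range cannot be attributed to unblinding. The share of outcome-led guesses is an assumption, shown over its whole range; the early-guess figures also assume a constant hazard. If guesses are unrelated to outcome, the check behaves as intended. The primary log-rank comparison is untouched. What changes is the conclusion that the trial can draw about assessor blinding.

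**What to change.** In the Guess-the-group section, alongside or instead of the single kappa:

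1. Report the proportion of correct guesses, or a blinding index, by arm.
2. Report agreement separately for patients with and without a reattempt.
3. State that a kappa above chance is not by itself evidence of failed blinding, and align the chance benchmark in {17a} with this.

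Optionally, have the assessor record the reason for the guess (patient disclosure, clinical course, other), and add a guess at the first post-therapy visit while keeping any later one. An early guess alone would miss unblinding during the 12-month follow-up, so it should not replace a late one.

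The cost is a change of wording and, for the options, one or two eCRF items. Intervals widen. For g1 − g0 with guesses near 50%, the 95% half-width is 1.96 × 0.5 × √(1/120 + 1/120) = 0.13 overall, 1.96 × 0.5 × √(1/96 + 1/72) = 0.15 among the 168 without a reattempt, and 1.96 × 0.5 × √(1/24 + 1/48) = 0.25 among the 72 with one. Stratifying by reattempt does not remove guesses driven by other clinical signs, such as suicidal ideation, so agreement left within strata suggests unblinding but does not prove it.

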##### Methods used to manage data that are missing, unused or invalid

For the primary analysis, the data are censored for the primary outcomes (SRFFP); it is not relevant to replace missing values. For the other outcomes, we do not have a replacement method for missing data.

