### Outcomes {12}

Following 6 weeks of interventional therapy, patients are followed up for 12 months by a psychiatrist. Follow-up for both groups is identical and includes the administration of questionnaires at baseline and then within 10 days after the end of GPACTS/IST sessions and then at 3, 6 and 12 months following the end of GPACTS/IST sessions. The primary outcome of interest for this study is the duration of time free of suicide reattempts. The null hypothesis for the primary outcomes for this study is that there will be no significant differences in the duration of a suicide reattempt-free follow-up period between the intervention and the control group.

Several secondary outcomes will be evaluated:

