##### Choice of patients to be included in the analyses

All patients included and randomized in the study will also be included in the analysis (intent-to-treat analysis). The conclusions of the study will be based on this analysis. Exploratory Per protocol analysis will be also performed.

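### The 12-month C-SSRS and reattempt yes/no models lose or misclassify patients lost to follow-up, although the plan already contains analyses that would keep them

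*Protocol article*

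**What the plan says.** The section on missing, unused or invalid data sets two rules. For the primary outcome: "For the primary analysis, the data are censored for the primary outcomes (SRFFP); it is not relevant to replace missing values". For everything else: "For the other outcomes, we do not have a replacement method for missing data". Both are repeated under item {20c}.

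The section on the choice of patients for analysis states: "All patients included and randomized in the study will also be included in the analysis (intent-to-treat analysis".

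Besides the duration of reattempt-free follow-up, the section on the principal endpoints names two further outcomes for multilevel modelling: "The suicide reattempt during the follow-up (yes/no) by adjusting for nested effects" and "The C-SSRS score at 12 months by adjusting for nested effects and C-SSRS score at inclusion". The section on secondary endpoints adds a longitudinal analysis: "Multilevel mixed-effects models will be used to assess treatment effects on the evolution of the C-SSRS score", and likewise for BSSI, BDI-II and BHS. After a baseline assessment, the questionnaires fall due as follows: "within 10 days after the end of GPACTS/IST sessions and then at 3, 6 and 12 months following the end of GPACTS/IST sessions".

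On loss, the sample size section says: "Taking into account an anticipated rate of 10% lost to follow-up, 240 patients will be included". Item {18b} sends the names of lost or deceased participants to the national cause-of-death register. Item {11b} keeps patients who stop therapy in follow-up.

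**The concern.** Having no imputation method is harmless where the analysis can use partial follow-up. It matters where the analysis needs a value that a lost patient cannot supply, and two of the listed models are of that kind.

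- **C-SSRS at 12 months, adjusted for baseline.** The response is one visit. Without that visit a patient contributes nothing, whatever was recorded at the end of therapy, 3 months or 6 months.
- **Reattempt yes/no.** A patient who reattempts before being lost is already a yes. A patient lost without an event has unknown status, and the article does not say whether such a patient is left out or counted as a no.

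In either model the analysed set is not the full randomised set, or some patients enter it with an assumed outcome. Patients here are at high risk and know their arm, so loss could plausibly be related both to outcome and to arm. At stake is the credibility of two supporting contrasts that readers will set beside the primary result.

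**Working it through.** **Inputs from the sample size section:** 240 patients, 120 per arm; 10% loss; 60% v 80% reattempt-free at 12 months, that is 40% v 20% with a reattempt.

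**Assumed, not in the document:** how loss splits between arms, and how much worse lost patients are.

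**1. The plan's own figures.** The pooled two-proportion formula gives, per arm, [1.960·√(2·0.7·0.3) + 1.036·√(0.6·0.4 + 0.8·0.2)]² / 0.2² = (1.2702 + 0.6555)² / 0.04 = 92.7. Rounded up this is 93 per arm, 186 in all, as stated. The step from 186 to 216 is an allowance for clustering without a stated intraclass correlation. 216 / (1 − 0.10) = 240, as stated.

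**2. Patients missing from the 12-month C-SSRS model.** 240 × 0.10 = 24, which leaves 216 (108 per arm if loss is equal). The loss of precision is small. The standardised difference detectable with 85% power, ignoring clustering, is (1.960 + 1.036)·√(2/n): 0.387 SD with n = 120 per arm and 0.408 SD with n = 108. The issue is bias, not power.

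**3. Bias in the C-SSRS contrast.** Let a fraction q of an arm be lost, with lost patients k SD worse than those observed. The observed mean then looks better than the full mean by q·k. The bias in the contrast is (q₁ − q₂)·k when k is the same in both arms.

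| Loss by arm | k = 1 SD | k = 2 SD |
|---|---|---|
| 10% v 10% | 0 | 0 |
| 15% v 5% | 0.10 SD | 0.20 SD |
| Deaths only, 3% v 1% | 0.02 SD | 0.04 SD |

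**4. Reattempt yes/no.** Take 12 patients per arm lost event-free and the design rates among the 108 observed: 0.4 × 108 ≈ 43 events on IST and 0.2 × 108 ≈ 22 on GPACTS.

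| Treatment of the lost | IST | GPACTS | Difference |
|---|---|---|---|
| Dropped | 43/108 = 39.8% | 22/108 = 20.4% | 19.4 points |
| Counted as no | 43/120 = 35.8% | 22/120 = 18.3% | 17.5 points |
| All lost on GPACTS reattempt, none on IST | 43/120 = 35.8% | 34/120 = 28.3% | 7.5 points |
| The reverse | 55/120 = 45.8% | 22/120 = 18.3% | 27.5 points |

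The last two rows are mathematical limits, not expected results.

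A milder illustration: lost patients have the same true risk as the others, all are lost event-free, and all are counted as no.

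- Loss of 15% on IST and 5% on GPACTS gives 0.40 × 0.85 = 34% v 0.20 × 0.95 = 19%, a difference of 15 points.
- The reverse loss gives 0.40 × 0.95 = 38% v 0.20 × 0.85 = 17%, a difference of 21 points.
- The true difference in both cases is 20 points.

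**5. The analyses already in the plan.** A likelihood-based mixed model of C-SSRS over the visits keeps patients who miss month 12 but were seen earlier, and is valid under missing at random without imputation. The Kaplan-Meier and log-rank analyses count each censored patient as at risk up to the time of loss. Neither has to drop these patients or guess their outcome.

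**The case against.** Much of the opposing case stands.

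- No replacement method means no imputation; it does not mean that loss is ignored. The longitudinal models of C-SSRS, BSSI, BDI-II and BHS handle intermittent and late loss under missing at random. A reader might infer that every outcome other than the primary is analysed on complete cases only; the document does not support that.
- Lack of imputation does not by itself breach intention to treat. Item {11b} uses the term for analysis by randomised arm with continued follow-up, and censoring keeps every randomised patient in the primary analysis. The mismatch is confined to patients without a value for the two models above.
- A reader might infer that suicides are excluded from the C-SSRS comparison. The text nowhere says so. It follows only as an inference from a 12-month score that a deceased patient cannot have, and cause of death is traced through the register.
- Non-informative censoring is the standard assumption of the log-rank test. Sensitivity checks on it are commonly left to the analysis plan, which the article announces, so their absence is no fault here.
- Both affected outcomes are supporting. The Outcomes section names reattempt-free time as the primary outcome and lists C-SSRS among the secondary ones.

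What the objection does not remove is that the missing-data rule is a stated decision, made twice, and that the two models are named. The issue is therefore a chosen method that discards or misclassifies patients, when analyses already in the plan would not.

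**Conclusion.** The point holds for two supporting analyses, C-SSRS at 12 months and reattempt yes/no, and only for those. At the planned 10% loss about 24 of 240 patients, plus any deaths not counted in that loss, leave the C-SSRS model. Those lost event-free have unknown yes/no status. This does not fit the stated inclusion of all randomised patients.

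The size of any bias depends on assumptions that the document cannot settle. It is nil for C-SSRS if loss is equal and similar by arm. It is about 0.1 SD under the assumed 15% v 5% loss with lost patients 1 SD worse, against a detectable difference of about 0.4 SD. For yes/no, with equal 10% loss and the design rates among those observed, the choice between dropping patients and counting them as no moves the difference from 19.4 to 17.5 points.

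The primary log-rank conclusion is not put in doubt by this point. It would be wrong to cite the 7.5-to-27.5-point limits as a likely error.

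**What to change.** In the detailed statistical plan, which is due before data extraction and unblinding:

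1. Estimate the month-12 C-SSRS contrast from the repeated-measures mixed model already planned for the secondary endpoints. Use all visits, keep the nesting terms, and state the missing-at-random assumption. This replaces the single-time-point model.
2. Report the 12-month reattempt difference from the time-to-event analysis, with clustering handled as in the planned multilevel model of reattempt-free time. Use it in place of the yes/no model or ahead of it. If the yes/no model is kept, for example for its intracluster correlation estimate, say how patients lost event-free are coded.
3. State how deaths by suicide, including those found through the register, enter each of these analyses. Without such a statement the mixed model treats scores after death as merely unobserved.
4. Amend the two missing-data statements so that they agree with the inclusion of all randomised patients.

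A sensitivity analysis for informative censoring of the primary outcome is optional and can be left to the analysis plan.

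The cost is revised wording and a little more analysis work. No new data are needed. The C-SSRS estimate will rest on missing at random, and the reattempt estimate on non-informative censoring, as the primary analysis already does.
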